## Mental wellbeing

A recent systematic review (Brazier 2014) found that the EQ-5D and SF-6D, while capturing changes in quality of life due to mental and physical illness, were less good at capturing other important aspects, including control, autonomy and choice; self-perception; belonging; activity; and hope. We will therefore use the Warwick-Edinburgh Mental Wellbeing Scale (WEMWBS) (Stewart-Brown 2011) as an additional secondary outcome measure, since this measures both subjective experiences of happiness and life satisfaction (the 'hedonic perspective'); and positive psychological functioning, good relationships with others and self-realisation (the 'eudaimonic perspective'). The latter includes capacity for self-development, positive relations with others, autonomy, self-acceptance and competence.

Coming off long-term antidepressants might improve these aspects of wellbeing, since side effects can include emotional blunting which should be reduced, and a greater sense of autonomy and self-acceptance might result from not having to rely on medication. WEMWBS has been shown to be responsive to change with a range of mental health interventions in specialist and community populations (Maheswaran 2012).

## Antidepressant withdrawal symptoms

These will be measured using the Discontinuation Emergent Signs and Symptoms Scale (DESS), a brief self-report measure on which participants can indicate the presence of, and changes in, 43 possible antidepressant withdrawal symptoms (Rosenblum 1988). Withdrawal symptoms will be measured at 3 and 6 months, asking patients to rate their presence looking back over the period since recruitment.

## Antidepressant side effects

These will be measured at baseline, 6, and 12 months (for those patients still taking antidepressants at follow-up), using the Antidepressant Side-Effects Check-list (ASEC) developed by Aitchison, as part of the GENDEP research project (<http://gendep.iop.kcl.ac.uk/results.php>). It asks participants to rate the presence of 21 possible side effects and also includes open questions for other symptoms not listed, and demonstrates good agreement between self-report and psychiatrists' ratings (Uher 2009).

At baseline, 6 and 12 months, we will also use the Changes in Sexual Functioning Questionnaire (CSFQ-C), a 14-item self-rating instrument including five domains of sexual functioning, which has been shown to be reliable and valid in both clinical and research settings (Clayton 1997; Keller 2006).

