## Outcome measures

The primary outcome for the main trial (WS5) will be the PHQ-9 score at 6 months, and secondary outcomes will include discontinuation of antidepressants; mental wellbeing; antidepressant withdrawal symptoms; antidepressant side effects; patient satisfaction; patient enablement; quality of life; and costs.

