## Quality of life

We anticipate that successful tapering and cessation of treatment will improve patients' quality of life (QoL) by reducing the adverse effects associated with taking antidepressants, along with the other burdens of unnecessary treatment including GP appointments and pharmacy visits.

We will measure QoL using the EuroQol-5D (EQ-5D)-5L. The EQ-5D-5L is the measure favoured by NICE in determining cost-effectiveness when developing its clinical guidelines. The EQ-5D-5L includes five dimensions: mobility, self-care, usual activities, pain/discomfort, and anxiety/depression, each scored on five levels (no problems, slight problems, some problems or severe problems and extreme problems). It is an improved version of the original EQ-5D-3L which was developed to reduce ceiling effects experienced with the EQ-5D-3L. We will apply the UK value set and scoring algorithm to translate EQ-5D-5L scores to utility scores (Devlin 2016).

We will also assess quality of life using the Medical Outcomes Study-derived measure of functional health status, the 12-item Short Form (SF-12) (Ware 1996), from which utilities can be derived using the SF-6D (Brazier 2004). One reason for using both measures is that the SF-6D may be more sensitive to changes in quality of life related to mild depression than the EQ-5D-5L (Peasgood 2012). We also do not know which measure will be more sensitive to changes in quality of life resulting from relief from antidepressant side effects on the one hand, or withdrawal symptoms on the other, resulting from antidepressant discontinuation. We therefore propose to use the SF-12 in addition to the EQ-5D-5L in WS5 and explore the implication of quality of life gained or loss in our study population in a sensitivity analysis.

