| Withdrawal symptoms (DESS)                                                                                     |   |   | ✓ | ✓ | ✓ |             |   |
| Antidepressant side effects (ASEC, CSFQ-C) (if taken)                                                          |   |   | ✓ |   | ✓ |             | ✓ |
| Satisfaction (MISS-29)                                                                                         |   |   |   |   | ✓ |             | ✓ |
| Enablement (PEI)                                                                                               |   |   |   |   | ✓ |             | ✓ |
| Questionnaires on use of services, use of antidepressants, sickness absence, and beliefs about antidepressants |   |   | ✓ |   | ✓ |             | ✓ |
| Collective efficacy questionnaire                                                                              |   |   |   | ✓ |   |             |   |

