## STATISTICAL ANALYSIS

Intention to treat (ITT) analyses at patient level will be performed, using mixed logistic/linear regression models, controlling for baseline values, stratification variables, and potential confounders as appropriate. Practice will be modelled as a random effect to allow for the clustering of patients within practices. Patterns of missing data will be explored, sensitivity analysis used to explore the impact of missingness, and imputation of missing data will be used. In a non-inferiority trial where some patients do not comply with treatment as randomised, the difference between the arms can appear reduced and the groups look more similar, leading to the incorrect conclusion of non-inferiority. A per protocol (PP) analysis would analyse individuals based on their compliance with treatment as randomised, excluding non-compliant participants, giving a more conservative estimate of effect for non-inferiority (Piaggio 2006).

However, the exclusion of some participants after randomisation can potentially lead to bias. Therefore we will present both ITT and PP analyses.

We will also undertake a complier-average causal effect (CACE) analysis, another approach to dealing with noncompliance that compares compliant participants in the intervention group, with those in the control group whose characteristics are similar enough to the intervention group compliers to suggest they too would have complied with the intervention, given the opportunity to do so (Angrist 1996, Dunn 2005). Compliance for these analyses in the intervention arm will be defined as completing the first session of the LifeGuide programme within 6 months of recruitment (anticipating 90% plus). The first session will have information about antidepressant treatment, the rationale for attempting withdrawal, and how withdrawal should be attempted under supervision. We would expect patients to benefit from that session even if they do not log on again. Compliance in the control arm will be defined as having consulted the GP/PN to have their antidepressant treatment reviewed within the 6-month follow-up period. For the primary outcome we will report the analyses based on all three approaches and interpret the findings cautiously in light of any differences between approaches that may emerge. This analysis will form the core of the publication of the trial results. No interim analyses will be performed.

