For secondary outcomes the analyses will use a similar modelling approach to that set out for the primary outcome, with mixed logistic/linear regression models as appropriate, with a random effect for Practice, controlling for baseline values, stratification variables, and potential confounders as appropriate. Discontinuation of antidepressants will be evaluated at the 6 month time point. All other secondary measures will be analysed using a repeated measures approach with measures clustered within patients over time in addition to the clustering of patients within practice. The models will control for stratification variables, and potential confounders as appropriate and, where a baseline measure for the outcome is available, will for the baseline value, too.

A detailed statistical plan will be developed and discussed with the Independent Data Monitoring Committee and Programme Steering Committee (see below).

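### The side-effect checklist (ASEC) is collected at 6 and 12 months only from patients still on antidepressants, so the between-arm comparison implied by the protocol conditions on a status the intervention is meant to change

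*Combined protocol and SAP*

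**What the plan says.** The protocol's Outcome measures section includes side effects in its list of secondary outcomes: "antidepressant side effects; patient satisfaction; patient enablement; quality of life; and costs". Under Antidepressant side effects, the ASEC follow-up is limited to current users: "These will be measured at baseline, 6, and 12 months (for those patients still taking antidepressants at follow-up". The row in the Consent and data collection summary carries the same limit and applies it to two instruments: "Antidepressant side effects (ASEC, CSFQ-C) (if taken". The text on sexual functioning has no such limit: "At baseline, 6 and 12 months, we will also use the Changes in Sexual Functioning Questionnaire (CSFQ-C".

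The protocol's Statistical Analysis section starts from patient-level ITT ("Intention to treat (ITT) analyses at patient level will be performed"). Apart from discontinuation, which is assessed at 6 months, it then says: "All other secondary measures will be analysed using a repeated measures approach". It gives no rule for the side-effect scores of patients who have stopped.

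The Quality of life section expects stopping to help partly "by reducing the adverse effects associated with taking antidepressants", and also by removing other burdens such as appointments and pharmacy visits.

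SAP 1.4.2 lists discontinuation at 6 months as a secondary endpoint. It lists neither ASEC nor CSFQ-C.

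**The concern.** Randomisation makes the arms comparable as whole groups. It does not make those still on the drug in one arm comparable with those still on it in the other, because the intervention works by moving patients out of that group. Two problems follow on this measure.

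- Patients who stopped, and who may have lost their side effects by stopping, have no follow-up value, so that relief is never recorded.
- If the chance of stopping depends on side-effect burden, the remaining users differ between arms through selection alone.

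The primary hypothesis is non-inferiority on PHQ-9, so the argument for adopting the intervention leans on the benefits of stopping. Collection is also uneven: withdrawal symptoms (DESS, at 3 and 6 months) are asked without regard to drug status, while side effects are asked only of those who did not stop. Data not collected at the visit cannot be recovered at analysis.

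**Working it through.** The documents give no target difference, SD or power for side effects, so there is no stated figure to reproduce. The check has three steps.

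**1. Passages side by side**

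| Element | Where | What it implies |
|---|---|---|
| Side effects are a secondary outcome | Protocol, Outcome measures | A between-arm result is expected |
| Repeated-measures models within an ITT framework | Protocol, Statistical Analysis | Comparison of arms as randomised |
| ASEC at 6 and 12 months from current users only | Protocol, Antidepressant side effects; schedule | Only a post-randomisation subset has data |
| Discontinuation is an endpoint | Protocol, Outcome measures; SAP 1.4.2 | The subset is defined by another trial outcome |

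The first two rows cannot be met with data collected under the third. A likelihood-based repeated-measures model does not repair this. Treating stoppers' scores as missing at random in effect predicts them from patients who stayed on the drug, which again leaves out the effect of stopping.

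**2. How many patients lack data by design**

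Inputs: 360 patients, 1:1; 20% non-compliance and/or loss, treated here as all loss; 7% control discontinuation (protocol, Control arm). The intervention rate is not given, so 20% to 50% is assumed.

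Followed up per arm = 360/2 × (1 − 0.20) = 144. Missing by design = 144 × discontinuation rate.

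| Arm and rate | Missing by design | With ASEC |
|---|---|---|
| Control, 7% | 10.1 | 133.9 |
| Intervention, 20% | 28.8 | 115.2 |
| Intervention, 30% | 43.2 | 100.8 |
| Intervention, 40% | 57.6 | 86.4 |
| Intervention, 50% | 72.0 | 72.0 |

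These counts equate being off the drug with discontinuation. The protocol counts discontinuation only after two months off, whereas the ASEC rule drops anyone not taking the drug at the visit, so the excluded group may be larger.

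**3. What the comparison would then show (illustration)**

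Assume that stopping lowers a side-effect score by 0.5 SD and that staying on the drug changes nothing. The all-patient difference, intervention minus control, is −0.5 × (p − 0.07), where p is intervention discontinuation:

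- p = 20%: −0.5 × 0.13 = −0.065 SD
- p = 40%: −0.5 × 0.33 = −0.165 SD
- p = 50%: −0.5 × 0.43 = −0.215 SD

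The difference among remaining users was simulated (2 million draws). The log-odds of stopping changed by a fixed amount per SD of burden, the same in both arms, with no baseline adjustment:

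| Log-odds of stopping per SD of burden | p = 20% | p = 40% | p = 50% |
|---|---|---|---|
| −0.7 (lower burden stops more) | +0.083 | +0.205 | +0.267 |
| −0.35 | +0.044 | +0.112 | +0.145 |
| 0 (unrelated) | 0.000 | 0.000 | 0.001 |
| +0.35 | −0.044 | −0.111 | −0.145 |
| +0.7 (higher burden stops more) | −0.083 | −0.205 | −0.267 |

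With no selection, the relief is invisible (the 0.001 is simulation noise). With selection, a difference appears in either direction. The 0.5 SD benefit does not enter the remaining-user figures at all, so the same differences would arise if stopping did nothing for side effects. Even the negative values, which point the same way as the assumed benefit, are not evidence of it.

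**The case against.** **A patient off the drug has no drug side effects.** Items endorsed off the drug may reflect withdrawal or mood, and side effects among users is a legitimate question. This stands as a reason for a descriptive summary of users and for care in reading off-drug scores. It does not support an arm comparison. ASEC rates the presence of 21 symptoms, which can be answered off the drug, and if stoppers were meant to score zero the plan would have to say so.

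**Baseline adjustment deals with selection.** It would help where stopping depends on baseline burden, so the simulated selection differences may be too large for an adjusted model. It cannot restore relief that was never measured.

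**Remaining users who are tapering may feel some relief.** They may, and then the comparison would not be exactly zero. That would show dose reduction, not stopping.

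**Stronger readings.** A reader might infer that the trial cannot show any benefit of stopping. The documents do not support that. EQ-5D and SF-12 (baseline, 3, 6, 9 and 12 months) and WEMWBS (baseline, 6 and 12 months) have no drug-status limit. The protocol chose them partly with relief from side effects and emotional blunting in mind. They are indirect, however, and the protocol says it does not know whether EQ-5D-5L or SF-12 is more sensitive to such relief.

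A reader might also infer that CSFQ-C is restricted in the same way. Only the schedule says so; the text does not, so this is a contradiction to reconcile.

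Finally, a reader might infer that the SAP commits to a biased analysis. It does not, since it plans no side-effect comparison. The problem arises from the protocol's secondary-outcome list and analysis section. The SAP's silence leaves a protocol outcome without an analysis and does not change what is collected.

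**Conclusion.** The point holds for ASEC as a direct measure of side effects. Under the stated collection rule, the comparison implied by the protocol is restricted to a group shaped by the intervention. Relief from side effects through stopping cannot appear on it, and any difference among remaining users may be selection of unknown sign. That structural fault depends on no assumed number.

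The sizes are illustrative. About 10 control against 29 to 72 intervention patients missing by design rests on an assumed 20% to 50% intervention discontinuation and on counting the planned 20% as loss. The 0.04 to 0.27 SD selection differences, in either direction, rest on assumed selection strengths. The documents give no intervention-arm discontinuation rate and no side-effect scores.

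The primary endpoint and the discontinuation endpoint are unaffected. The plan should be changed, but the trial's main conclusion does not turn on it. Two reconciliations go with it: CSFQ-C text against schedule, and the protocol's secondary outcomes against SAP 1.4.2.

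**What to change.** - **Collection.** Give ASEC and CSFQ-C to every patient at 6 and 12 months whatever their antidepressant status. Delete the restriction in the Antidepressant side effects section and the qualifier in the schedule row, which also settles the CSFQ-C conflict.
- **SAP.** List both in 1.4.2 and analyse them by randomised arm with the 4.5 repeated-measures model, adjusted for baseline. Keep a summary of those still taking the drug as descriptive only.
- **Visits already completed under the current rule.** The May 2021 sample-size review used 6-month data, so follow-up was already under way by then. Report how many visits are affected in each arm, treat the absent values as missing by design, and state that the comparison is limited.

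Cost: protocol and form wording, and a few extra minutes at visits already scheduled. The main downside is interpretation, because off-drug ASEC items may reflect withdrawal or mood symptoms. They can be read alongside DESS at 6 months only, since DESS is not collected at 12 months.

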## Patient satisfaction

We will assess this using the 29-item 'Medical Interview Satisfaction Scale' (MISS-29) which was developed in the USA to assess patient satisfaction with individual doctor-patient consultations and has been shown to be valid and reliable in UK primary care (Meakin 2002). We will adapt it to rate patient satisfaction at the 6-month follow-up, asking patients to look back over their consultations with the GPs/PNs for advising on tapering and cessation of antidepressants.

## Beliefs about antidepressants

A bespoke questionnaire asking for patients' beliefs about antidepressants, and their cessation, developed by a Southampton PhD student [name], will be administered at the face-to-face assessments at baseline, 6 months and 12 months. This will enable a mediator analysis of possible effects of changes in patients' beliefs on changes in antidepressant use.

## Collective efficacy

At the 3-month assessment point, we will administer the collective efficacy questionnaire (Band 2019) which is a measure of the strength of support for discontinuing antidepressants which a participant perceives among their important friends and family. The importance of this support as a possible moderator of the success of the intervention

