## Consent procedure

The researcher will arrange to meet the patient, either remotely, or at their GP practice, or at their home if they prefer, to go over the consent procedure. If the patient gives verbal and then subsequent written consent to take part, the researcher will conduct a baseline assessment. Information given at the point of consent will be the same in both arms. All patients will be told we are recruiting people who have been taking antidepressants for more than a year for a first episode, or more than two years for a recurrent episode, with a view to working out how to help them reduce their medication if appropriate, with the advice of their practice GP or nurse (see patient information leaflet and consent form). The information leaflet will outline the two different approaches but not in detail and potential participants will not know to which arm their general practice has been randomised. This is to avoid differential rates of consent to the two arms based on patients' opinions of the intervention or procedures involved in each.

Patients who do not wish to consent to take part at that point for reasons which may be temporary (i.e. they do wish to try to reduce and stop taking their antidepressant, but not at that time due to current life stresses, recent life events, or the timing of upcoming events etc.), will have the option of consenting to be re-contacted after three months, to be asked again if they wish to participate at that later point.

Having once consented to take part in writing on this initial basis, and having undergone baseline assessment, patients will then be given further information about the details of the procedures in the arm to which their practice has been randomised. In the intervention arm, patients will be given advice and support to log on and engage with their web-based support (see below). After looking at the on-line ADvisor for patients, they will be asked to arrange to consult with their GP/NP either remotely or in person to discuss coming off antidepressants, including agreeing a time to start tapering the dose, and a first follow-up appointment for review.

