## Intervention arm

The practitioner intervention (called 'ADvisor for Health Professionals' as it gives advice about AntiDepressants) includes Internet modules on: Why reduce; Broaching the subject; When to start tapering; Reduction schedules for individual antidepressants; Dealing with withdrawal symptoms; Dealing with relapse; ADvisor for patients (a summary); and printable pages on antidepressant reduction regimes and sections of ADvisor for patients to recommend patients consult.

The patient intervention (called 'ADvisor for Patients') includes Internet modules on: Reducing and stopping (introduction to website); How to reduce antidepressants; Thinking about antidepressants (their effects and why lifelong treatment may not be necessary); Dealing with withdrawal symptoms; I'm worried about stopping; Keeping well; Thinking about what you value in life; and Moving forward.

In the intervention arm practices, the GPs/NPs will be given access to the on-line ADvisor for practitioners, and induction to the study, which will be either practice-based or on-line. They will receive an introduction to ADvisor, and education on best practice in the supervision of antidepressant tapering and cessation, focussing on the differences between withdrawal symptoms and relapse, and the management of withdrawal symptoms.

The number and timing of subsequent GP/NP consultations during tapering and following drug cessation will be left to the participating GPs/NPs to agree with the patients on an individual basis.

In addition to the ADvisor Internet modules and GP/NP consultations, the following telephone support will be provided to patients in the intervention arm by a trained psychological practitioner (PP):

- Call 1 (0-2 weeks), for 30 minutes: to check the patient's understanding of the ADvisor intervention and encourage confidence in going through the tapering and cessation process
- Call 2 (4-6 weeks), for 15 minutes: to ask the patient how tapering is going and whether they are following the schedule, and where necessary, to advise the patient to discuss any issues with tapering with their GP
- Call 3 (timing agreed with patient), for 15 minutes: to ask the patient about any residual withdrawal symptoms and go over techniques to help with relapse prevention.

A sample of 10-20 telephone calls per practitioner will be audio-recorded in the first three months, and again halfway through the trial, to check for fidelity against the telephone support guise.

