## Discontinuation of antidepressants

Discontinuation of antidepressants will be deemed to have occurred once the patient has stopped taking them for two months. Determining discontinuation after six months will allow tapering and cessation to take up to four months. In our experience, after two months, withdrawal symptoms will have mostly gone, and mood problems will have re-emerged if they are going to. We think patients who decide to resume treatment are unlikely to wait even one month.

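### Collective efficacy is named as a possible moderator but is measured only at 3 months, after allocation is known; any moderation analysis would need a baseline score

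*Combined protocol and SAP*

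**What the plan says.** **Construct and timing.** The protocol section on collective efficacy describes the questionnaire as "a measure of the strength of support for discontinuing antidepressants which a participant perceives among their important friends and family". On timing it says: "At the 3-month assessment point, we will administer the collective efficacy questionnaire". In the consent and data collection summary, the row "Collective efficacy questionnaire" has one tick, at 3 months. Baseline and all later visits are blank.

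**Role.** The only statement of purpose is "The importance of this support as a possible moderator of the success of the intervention". In the text available to us the sentence stops there, and no analysis is described.

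**What happens before 3 months.**
- Consent procedure: "having undergone baseline assessment, patients will then be given further information about the details of the procedures in the arm".
- Intervention arm: two of the three support calls are timed before 3 months, "Call 1 (0-2 weeks), for 30 minutes" and "Call 2 (4-6 weeks), for 15 minutes: to ask the patient how tapering is going". The timing of the third is agreed with the patient.
- Discontinuation section: "Determining discontinuation after six months will allow tapering and cessation to take up to four months".

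**Analysis.** Collective efficacy is not among the SAP endpoints (1.4) or the covariates of the primary model (4.4). SAP 4.6 plans no subgroup analyses and treats post-hoc work as exploratory.

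**The concern.** A moderator analysis asks whether the intervention works better for some patients than for others, according to a characteristic they bring to the trial. The characteristic therefore has to be recorded before the allocation can act on it. Support perceived from friends and family can change. Someone whose taper is going well may come to see those around them as more supportive, and someone who is struggling may see the reverse. If that happens to a different degree in the two arms, the 3-month score carries information about treatment response in one arm that it lacks in the other. An arm-by-support interaction can then appear when support at entry made no difference to the treatment effect.

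The stake is modest but real. The process evaluation is meant to inform implementation, and a false signal could suggest that the intervention suits mainly well-supported patients. Without a baseline score, no later analysis can recover the pre-treatment value.

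**Working it through.** The plan gives no figure on this point, so there is none to reproduce. The check has two parts.

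**1. Order of events, from the protocol**

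| Event | Timing |
|---|---|
| Baseline assessment | before the patient learns the arm |
| Arm-specific procedures explained | after baseline |
| Call 1, intervention arm | 0–2 weeks |
| Call 2, intervention arm, asks about tapering | 4–6 weeks |
| Collective efficacy measured | 3 months |
| Period allowed for tapering and cessation | up to 4 months |
| Primary outcome and discontinuation | 6 months |

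Month 3 falls after disclosure and inside the period allowed for tapering. The score is post-allocation.

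**2. Can that timing create apparent moderation?**

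Inputs:
- Patients analysed: 360 × 0.8 = 288, or 144 per arm (target and 20% allowance from the sample size section; used only to size the illustration).
- Stopping in the control arm: 7% (protocol, Control arm).
- Stopping in the intervention arm: 25% (assumed; not in the documents).
- Feedback b from tapering progress to reported support: 0.2 to 0.5 SD per SD of progress (assumed).
- Clustering ignored.

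Model: progress P and baseline support M0 are independent standard normal. A patient stops if P exceeds the threshold that gives 7% or 25%. The 3-month score is M3 = M0 + b × P. Support at entry has no influence on stopping, so there is no true moderation. The test is the arm × M3 interaction at the 5% level.

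| Setting | Linear probability model | Logistic model |
|---|---|---|
| Feedback in intervention arm only, b = 0.2 to 0.5 | about 31–96% | about 13–51% |
| Equal feedback in both arms, b = 0.2 to 0.5 | about 14–53% | about 5% |
| Uniform shift in support, intervention arm | about 5% | about 5% |
| Baseline score used as moderator | about 5% | about 5% |

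Repeat simulations move these entries by a few percentage points.

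Hand check of the low end for the linear probability model, b = 0.2 in the intervention arm only. The expected slope of stopping on M3 is b × φ(z)/(1 + b²), with φ the normal density at the stopping threshold z.
- Intervention: z = 0.674, φ = 0.318, slope = 0.2 × 0.318/1.04 = 0.061. Control: slope 0.
- Standard errors: √(0.25 × 0.75)/(√144 × √1.04) = 0.433/12.24 = 0.035, and √(0.07 × 0.93)/√144 = 0.255/12 = 0.021. Combined: √(0.035² + 0.021²) = 0.041.
- Ratio 0.061/0.041 = 1.48, so the rejection rate is about Φ(1.48 − 1.96) = 0.32, in line with the simulated 31%.

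With equal feedback the control slope becomes 0.2 × 0.134/1.04 = 0.026. A gap of 0.035 remains on the risk-difference scale only because the stopping rates differ; the logistic model does not show it.

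**Second illustration, continuous outcome** (ordinary least squares, 288 patients, 2,000 runs, constant treatment effect, assumed effect sizes):
- 3-month score unaffected by the intervention: 5.4%.
- Score shifted equally for all intervention patients: 5.1%.
- Score raised more in intervention patients with better prognosis: 12.5% (smaller assumed effect) and 22.8% (larger).
- Outcome feeding back on support in the intervention arm: 57.4%.
- Baseline score: 4.7–5.4% throughout.

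Both illustrations give the same condition. The problem needs support to respond differently by arm or by prognosis.

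**The case against.** The strongest reply is that no moderation test is planned. The one sentence on purpose is incomplete, perhaps through text extraction, and says only that moderation is possible. The SAP has no such model, and the protocol's quantitative process section plans mediation analyses, for which a 3-month score is a natural candidate. This stands. A reader might infer that the trial is committed to testing collective efficacy as a moderator, or that its conclusions are at risk; the documents support neither.

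Second, the largest false-positive rates depend on choices made for the illustration: a 25% stopping rate, feedback confined to one arm, progress fully determining stopping, and a linear probability model where the plan uses mixed logistic regression for discontinuation. This also stands. A reader might take a third to nine-tenths as the expected error. Under the plan's model family the range is about 13–51% with intervention-only feedback and about 5% with equal feedback, and control patients may also taper.

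Third, it is not certain that every intervention patient has used the website or begun tapering by 3 months. Completion of the first session is anticipated at 90% or more, and the start of tapering is agreed individually. Hence the wording that tapering may be under way.

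Fourth, the beliefs questionnaire is given at baseline, and the psychological process section mentions related work on the perceived views of important others. That might serve as a partial proxy, but the documents do not say it will be used as a moderator, and it is not the collective efficacy measure.

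None of this removes the core point. Calling an analysis exploratory does not turn a post-allocation score into a pre-treatment one.

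**Conclusion.** The point holds as a minor one. The single 3-month score cannot serve as a clean moderator, which is the one role the protocol names for it. The risk is conditional: an analysis that the SAP does not specify would have to be run, and perceived support would have to respond differently by arm or by prognosis.

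Its size cannot be fixed from the documents. It runs from no inflation to a serious false-positive rate, depending on the assumed feedback and the model. No sample size or power figure changes. The primary outcome and the listed secondary outcomes do not use this score.

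**What to change.** - Add the collective efficacy questionnaire at the existing baseline visit, before the patient is told the arm, and use that score for any moderator analysis.
- Keep the 3-month administration and describe it as a possible mediator.
- For patients already past baseline, report the 3-month score only as an exploratory post-allocation correlate and make no moderation claim from it.
- State the intended analysis in the protocol section or in a process evaluation plan: the model and its scale (logistic for discontinuation), and that it is exploratory. If the sentence on the possible moderator is also incomplete in the source protocol, finish it at the same time.

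Cost: one short questionnaire at a visit that already takes place, so a few minutes of patient time, plus a small protocol amendment.
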